#### Data collection

Attending nurses will fill out data collection forms for each subject during admission. These forms will be used to enter data in a digital data capture programme (Research Manager). Once a subject is registered in Research Manager, digital questionnaires are automatically sent at the follow-up time points, with reminders after 1 week. If unanswered, patients will be contacted by telephone or text message to be reminded or to complete essential safety data questions by phone. Pseudonymisation is used to code the collected data, with only the local research team having access to the pseudonymisation key.

#### Data management and archiving

Data will be managed based on a data management plan that has been established for this project. Data will be collected and processed following the General Data Protection Regulation (EU) 2016/679. The clinical trial master file’s content, including data and source documents, will be archived for at least 25 years after the clinical trial’s conclusion.

#### Statistical methods

##### Primary study parameter(s)

The time to meet all discharge criteria will be presented in hours. The primary analysis will be conducted on an intention-to-treat basis. Point estimates and uncertainty will be chosen based on the distribution of the data. The difference in hours between the groups will be analysed and tested for statistical significance, adjusting for centre and age and using a multilevel linear regression model for hospitals, with diagnosis and patient clinical parameters at presentation as covariates. A 12-hour difference is deemed clinically significant. Sensitivity analysis will include a per-protocol analysis of the primary outcome. For other time-to-event parameters, a Cox proportional hazards model will be used to estimate the intervention effect.

##### Missing data

If the time to meet all discharge criteria is missing because the time of meeting any/all discharge criteria was not noted, the point-estimate difference between the time of meeting all criteria and the time of discharge in the recorded population will be subtracted from the time of discharge and used instead.If time to meeting all discharge criteria are missing because the child was transferred to the PICU, these patients are excluded from the primary analysis but included in the safety analyses.Missing data in the covariates will be investigated to identify the mechanism (missing not at random, at random or completely at random) and handled appropriately. The default approach will be to use multiple imputation with all data available on the subjects. A complete-case analysis will be performed as a sensitivity analysis.

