#### Control group

Patients in the control group will receive supplemental oxygen if:

Their SpO2 levels drop below 92%, by:1%–2% for at least 15 min continuously.>2% for any amount of time.When indicated by the treating physician for clinical symptoms.

Supplemental oxygen can be administered by either a face mask or nasal cannula, following local protocols. Patients are weaned of supplemental oxygen according to local protocols and based on the randomised SpO2 threshold.

Patients transferred to a paediatric intensive care unit (PICU) will receive standard care according to local PICU protocols, including SpO2 thresholds, and will be analysed according to protocol and included in the safety analyses.

To ensure adherence to the study protocol, both nurses and physicians at each centre will be trained to follow the study protocol. Any deviations from this protocol must be documented. Study protocol adherence is monitored by the registration of start and stop times of supplemental oxygen administration, including the reasons for starting and stopping, and clinical symptoms of the patient such as respiratory rate, heart rate and work of breathing. All other care is as usual. There are no prohibited concomitant care activities, drug prescriptions or interventions.

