### Outcomes

#### Primary outcome

The primary outcome of this trial is the time from admission to when all prespecified discharge criteria are met. Prespecified discharge criteria are:

No need for supplemental oxygen for 4 hours, including a period of sleep for children aged <2 years.Clinically fit for discharge with normal or minimally increased respiratory rate AND no or mild respiratory distress, as judged by nurses and physicians using the Parshuram *et al*^15^ scoring system, commonly used in Dutch paediatric practice as part of the Paediatric Early Warning Scale.^16^No need for in-hospital feeding or medication by nasogastric tube.No need for in-hospital intravenous treatment.No need for in-hospital nebulised bronchodilator treatment.No need for in-hospital treatment with metered dose inhalator inhalations more often than every 3 hours.No need for high flow delivered by high flow nasal cannula or nasal prongs.

Nursing staff continuously monitor discharge criteria and register them when met. Clinical fitness for discharge is checked every 4 hours, starting 4 hours after oxygen therapy is first stopped. If oxygen therapy is not initiated, this criterion is checked every 4 hours starting 4 hours after randomisation. In clinical practice, the actual discharge time may be later than when all discharge criteria are met. The reasons for any delay in discharge will be documented.

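### The fill-in rule for a missing primary time can produce values the outcome definition rules out and, read literally, also covers children who left with a criterion unmet

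*Protocol article*

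**What the plan says.** The primary outcome runs from admission until the last of seven discharge criteria is satisfied (protocol article, Primary outcome). The first criterion requires 4 hours without oxygen need, with a sleep period for children under 2 years. On recording, the section says: "Nursing staff continuously monitor discharge criteria and register them when met". On the order of events it says: "In clinical practice, the actual discharge time may be later than when all discharge criteria are met". It does not mention a child leaving before all criteria are met.

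The Missing data section names two causes of a missing primary time.

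- **Time not noted.** The trigger is "If the time to meet all discharge criteria is missing because the time of meeting any/all discharge criteria was not noted". The quantity used is "the point-estimate difference between the time of meeting all criteria and the time of discharge in the recorded population", and it "will be subtracted from the time of discharge and used instead".
- **PICU transfer.** Here "these patients are excluded from the primary analysis but included in the safety analyses".

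The primary analysis is intention-to-treat, with a multilevel linear regression on hours (Primary study parameter(s)). Adherence monitoring includes "registration of start and stop times of supplemental oxygen administration" (end of the Control group section).

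**The concern.** Criteria are registered only when met, so a criterion that was never met before the child left has no time. The trigger does not separate a criterion that was met but not written down from one that was not met. For a child who did not go to a PICU, the subtraction is the only stated rule that could apply. It returns a completed time at or before discharge, when all that is known is that the true time lies after discharge.

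A second problem does not depend on how the trigger is read. One average gap is subtracted for every child, without checking the result against times the trial already holds. The filled-in value can then contradict the recorded oxygen stop or a criterion recorded later.

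The trial is open-label, and the threshold under test decides oxygen need, which is the first criterion. Leaving with that criterion unmet could therefore differ by arm. If it did, the primary difference would move for a reason unrelated to recovery.

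**Working it through.** **The plan's own figure.** Inputs from Sample size and feasibility: difference 12 h, SD 48 h, alpha 0.05 (taken as two-sided), power 80%.

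- n per arm = 2 × (1.960 + 0.842)² × (48/12)² = 2 × 7.849 × 16 = 251.2. The plan states 251, and power at 251 is 0.80.
- With 10% dropout, 502/0.9 = 557.8, so 558 against the stated 560.

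The sample size is sound and is not in question. It gives the yardstick used below: the standard error of the difference is 48 × √(2/251) = 4.3 h.

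**Direction of the error.** Let D be discharge, T the true time of meeting all criteria, g the subtracted gap and T* = D − g the filled-in time. The gap comes from children who met the criteria at or before discharge, so g ≥ 0 and T* ≤ D. For a child who left with a criterion unmet, T = D + r with r > 0, where r is the further time needed. The value is too early by T − T* = g + r.

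**Contradiction with recorded times.** Let S be the final recorded oxygen stop. The definition requires T ≥ S + 4. The rule breaks this whenever D − S < 4 + g.

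- *Criterion unmet.* A child leaves at S + 3. Then T* = S + 3 − g, at least 1 h before the earliest possible time for any g ≥ 0.
- *Recording failure only.* A child met everything at S + 4 and left at S + 6. With an assumed g of 4 h, T* = S + 2, which is 2 h too early to be possible.

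In general, a child whose own gap is shorter than the average gets a time before the true one. The contradiction is visible whenever the oxygen stop or another late criterion is on record.

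**Does another part of the plan repair it?** No censoring is stated for the primary outcome. Interval- and right-censoring appear only under Secondary study parameter(s). The multiple imputation and complete-case analysis in the Missing data section follow the sentence on covariates.

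**Size.** Shift in the arm difference = (p1 − p0) × (g + r), where p is the share of each arm leaving with a criterion unmet. The documents give none of these quantities, so every input here is assumed.

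| Imbalance in shares | Error 8 h | Error 18 h |
|---|---|---|
| 0 points | 0 h | 0 h |
| 5 points | 0.4 h | 0.9 h |
| 10 points | 0.8 h | 1.8 h |

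The top value is 1.8/12 = 15% of the target and 1.8/4.3 = about 0.4 of a standard error.

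Wider assumptions (g from 4 to 12 h, r from 0 to 24 h, so 4 to 36 h per child) give:

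| Shares | Shift | Largest type I error, no true difference |
|---|---|---|
| 2% v 2% | 0 h | 0.050 |
| 5% v 2% | 0.12 to 1.08 h | 0.057 |
| 10% v 5% | 0.20 to 1.80 h | 0.071 |
| 10% v 2% | 0.32 to 2.88 h | 0.103 |

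Using discharge time removes only the g part. At 10% v 5% that is 0.05 × 4 to 12 = 0.2 to 0.6 h; the r part, 0.05 × 0 to 24 = 0 to 1.2 h, stays.

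**The case against.** The ordinary meaning of a time that was not noted is a recording failure. Nowhere does the article say that a child with an unmet criterion receives the subtraction. On that narrower reading such a child simply has no rule, and a condensed article may leave the case to the full protocol or SAP, which are not shown. This stands as far as it goes. It does not touch the impossible values after a recording failure, nor the fact that the published trigger is worded widely enough to catch the other case.

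The affected group may be small. Four of the seven criteria concern in-hospital feeding or treatment, and clinical fitness is judged by staff, so a child sent home by clinicians will usually satisfy these. What remains is mainly the oxygen-free period with its sleep requirement, respiratory status, transfers and removal by parents. This stands.

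The existing data would identify many such children: oxygen times with reasons, documented deviations and condition at discharge. A per-protocol sensitivity analysis is also planned. This stands too, and it makes the correction cheap, but it does not alter the values entering the primary analysis.

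The likeliest example, a control child at 90–91% whom staff consider well, would shorten control-arm time and pull the result towards no difference. No mechanism that would inflate the effect is documented. The net direction is therefore open.

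**Conclusion.** The point holds as a defect in a stated rule, not as a demonstrated bias. Two things are certain: the rule can return times that the outcome definition excludes, and for any child with an unmet criterion to whom it were applied, the error has the wrong sign.

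A reader might infer more: that the plan takes discharge always to follow the criteria, that it does score early leavers as successes, or that the primary result is materially biased. The documents support none of these. They say only that discharge may be later, they never expressly apply the subtraction to an unmet criterion, and they give no count of such children.

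The shift in the difference is zero with equal shares. Under the assumed 5 to 10 point imbalance and 8 to 18 h error it is 0.4 to 1.8 h, at most about 0.4 of a standard error. The largest figures in the working need 10% of one arm to leave with a criterion unmet, for which there is no evidence. The change is still worth making because it costs little and nothing else stated for the primary analysis corrects these values.

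**What to change.** Amend the Missing data section as follows.

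1. Limit the subtraction to children who met all criteria but whose time was not recorded.
2. Let no filled-in time precede the recorded oxygen stop plus 4 hours or the latest recorded criterion time.
3. For a child who left, not to a PICU, with a criterion unmet, use the discharge or transfer time, or the floor in (2) if later, as a lower bound in the primary linear model. Identify these children from oxygen times, deviation records and condition at discharge. Add a sensitivity analysis that right-censors at that time; this needs a censored-data model, because the planned linear regression cannot do it. Report the number of such children by arm.

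**Cost.** A few sentences, one extra model and one extra count, all from data already collected. There are three downsides. The lower bound still understates the true time by r. The floor brings each value it changes closer to the truth but only ever moves values later, so the filled-in times rise slightly on average. Recruitment began on 7 September 2023, so children already enrolled can be classified only from existing records, and a missing sleep period may not be traceable there.

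### An unrecorded primary time is replaced by discharge time minus one lag with no arm term, which biases the hours difference if the discharge lag differs by arm

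*Protocol article*

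**What the plan says.** The primary outcome is the time from admission until all seven listed discharge criteria are met. Under Primary outcome the article separates this from actual discharge: "In clinical practice, the actual discharge time may be later than when all discharge criteria are met". It adds that reasons for delay are documented. Length of stay to discharge is a separate secondary outcome.

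Under Missing data there is a specific rule for a primary time that is "missing because the time of meeting any/all discharge criteria was not noted". In that case a point estimate of the difference between meeting all criteria and "the time of discharge in the recorded population will be subtracted from the time of discharge and used instead", so the result stands in for the observation. The rule has no term for arm, centre or patient. Whether the point estimate is a mean or a median is not fixed; Primary study parameter(s) says only that "Point estimates and uncertainty will be chosen based on the distribution of the data".

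The same section treats covariates differently. It opens that item with "Missing data in the covariates will be investigated to identify the mechanism" and continues "The default approach will be to use multiple imputation with all data available on the subjects". A complete-case sensitivity analysis follows in the same item, so it is unclear whether it also covers children whose primary time was filled in.

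Two other statements bear on the point. The Randomisation and allocation procedure section says that participants, physicians and research staff are not blinded. The Control group section provides for "registration of start and stop times of supplemental oxygen administration", so oxygen stop times will be available.

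**The concern.** How long a child stays after meeting the criteria is partly a decision by staff who know the allocation. A child in the 88% arm can satisfy the oxygen criterion at a saturation that would call for oxygen in the 92% arm, and staff may then be slower, or quicker, to send that child home. If so, the lag differs by arm.

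A constant shared by both arms cannot represent such a difference. It cancels from the contrast (exactly so when missing shares are equal), and the imputed children contribute a difference in discharge times in place of a difference in times of meeting the criteria. Discharge lag, which the primary outcome is defined to leave out, returns through those children.

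The rule also sets aside recorded information. One un-noted criterion time is enough to trigger it, even if the other six are recorded, and neither oxygen stop times nor reasons for delay are used. For a child discharged promptly, subtracting an average lag can give a time earlier than 4 hours after the last oxygen stop, which the first discharge criterion rules out.

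**Working it through.** **The plan's own figure.** Inputs from Sample size and feasibility: difference 12 h, SD 48 h, alpha 0.05 (two-sided assumed), power 80%. n per arm = 2 × (1.960 + 0.842)² × 48² / 12² ≈ 251.2, against 251 stated (252 if rounded up). Dropout: 502 / 0.90 = 557.8, against 560 stated. The figures reproduce, and power at 251 per arm is 0.80. The design therefore has no margin if the effect is diluted.

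**Bias of the rule.** Let T be the true time, L the lag, D = T + L the discharge time and c the constant. The imputed value is D − c = T + (L − c). With missing share m and mean lag L in each arm, and times missing at random within arm:

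bias in (88% − 92%) = m88 × (L88 − c) − m92 × (L92 − c).

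With equal missing shares c drops out:

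bias = m × (L88 − L92).

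With unequal shares and c the mean over all recorded children:

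bias = (L88 − L92) × [m88(1 − m92) + m92(1 − m88)] / [(1 − m88) + (1 − m92)].

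For 10% and 20% missing and a 4 h lag difference this is 4 × (0.08 + 0.18) / 1.70 = 0.61 h.

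**Size.** The document gives no missing shares or lags, so these are assumptions. Power uses SE = 48 × √(2/251) ≈ 4.28 h and a true benefit of 12 h, with the longer lag in the 88% arm.

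| Missing, both arms | Lag difference | Bias | Effect left | Power |
|---|---|---|---|---|
| 5% | 2 h | 0.1 h | 11.9 h | 0.79 |
| 10% | 4 h | 0.4 h | 11.6 h | 0.77 |
| 20% | 4 h | 0.8 h | 11.2 h | 0.74 |
| 30% | 6 h | 1.8 h | 10.2 h | 0.66 |
| 30% | 12 h | 3.6 h | 8.4 h | 0.50 |

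If the 92% arm has the longer lag, the same amounts are added to the apparent benefit.

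**Simulation.** 6,000 trials per scenario, 251 per arm, lognormal times, exponential lags independent of time, missing at random, unadjusted difference in means, true difference −12 h.

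| Missing; lags 88% v 92% | Shared constant | Arm-specific constant |
|---|---|---|
| 10%; 10 v 6 h | −11.6 h | −12.0 h |
| 20%; 10 v 6 h | −11.2 h | −12.0 h |
| 30%; 12 v 6 h | −10.3 h (power 0.67) | −12.1 h (power 0.80) |

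With no true effect, 20% missing and lags of 10 v 6 h gave a mean estimate of 0.8 h and 5.5% rejections. With 30% missing and lags of 6 v 12 h the figures were −1.7 h and 6.2%.

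**Standard error.** With 10–30% missing and the shared constant, the ratio of model to empirical standard error was 0.99–1.02. Coverage with equal lags was 0.95–0.96.

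**Mean or median.** With equal lags (mean 6 h), a median constant and 5% v 25% missing, the estimate was −12.4 h. That is a further bias of about 0.4 h, which arises only because the choice of estimate is left open and missing shares differ.

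**The case against.** The strongest reply is that the bias is small and every input to it is assumed. Nursing staff are to monitor and register the criteria continuously, so heavy missingness is not to be expected, and nothing in the document shows that lags differ by arm. At up to 20% missing and a 4 h lag difference the bias stays under 1 h, and false rejection barely moves. This stands, and it limits the weight of the point.

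It can also be said that pooling over arms is inferred, since the text refers only to the recorded population, and that an article condenses the full protocol. The inference is fair to flag. But the article does more than leave the matter open: it states a rule, and as written that rule has no arm term.

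Two partial safeguards exist: the complete-case analysis and the separate analysis of length of stay. The first has unclear scope. The second is a useful cross-check, but neither corrects the primary estimate.

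A reader might infer three stronger things that the document does not support.

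- That single imputation makes the standard error too small. Here it does not: each imputed value keeps the child's own discharge time, so lag variation stays in the residual variance, and error in a shared constant largely cancels between arms.
- That the trial rejected length of stay as primary outcome because of discharge lag. The article acknowledges the lag but gives no such reason.
- That oxygen stop plus 4 hours bounds every child's time. The Primary outcome section provides for children in whom oxygen is never started, and they have no stop time. How often the rule would give an impossible value is also unknown.

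**Conclusion.** The point holds as a bias in the primary estimate. The stated rule fills an unrecorded time with discharge time minus one lag that ignores arm, and if lags differ by arm the hours difference is off by about the missing share times the lag difference. It becomes material to a 12 h target only when missingness and the lag difference are both large. The direction cannot be known in advance, so the rule could dilute or exaggerate a benefit of the 88% threshold. This rests on reading the recorded population as both arms together, on times missing at random within arm, and on assumed missing shares and lags. It is worth correcting because a better method is available from data already collected.

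**What to change.** Multiply impute the missing time of meeting all criteria, or equivalently the lag, with arm in the imputation model. Include discharge time, oxygen stop time, documented reason for delayed discharge, centre, age group, diagnosis and baseline severity. Bound the imputed time above by discharge. Bound it below by last oxygen stop plus 4 hours where oxygen was given and, for children never started on oxygen, by the first fitness check, which the article places 4 hours after randomisation. Pool with Rubin's rules.

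At minimum, compute the lag separately by arm and fix in advance whether it is a mean or a median. Keep the single-constant rule as a sensitivity analysis, and state that the complete-case analysis also covers children with an imputed primary time.

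The cost is a change of wording and a little more analysis work. Multiple imputation is already planned for covariates, and the main predictors are already collected.

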#### Safety outcomes

Number of PICU admissions.Number of unscheduled readmissions and revisits to healthcare providers, as reported by parents in follow-up questionnaires and registered from patient electronic health records.Duration of symptoms, defined as time in days from admission to meeting the following criteria:Resolution of cough (less than one cough every hour), as reported by parents.Resolution of dyspnoea, as reported by parents.Cessation of scheduled salbutamol use, as reported by parents.Time in days from admission to return to normal health, as reported by parents.Time in days from admission to return to school/day care, as reported by parents.Patient quality of life during follow-up, measured by digital questionnaires at discharge, 7 days, 28 days and 90 days after discharge by EuroQol Five Dimensions Health Questionnaire Youth (EQ-5D-Y) (by patient or by parent proxy form). For ages 6 weeks to 2 years, only the EuroQol Visual Analogue Scale (EQ-VAS) is used, as this is the only tool with good clinimetric properties in this age group which can be compared with the full 6 weeks to 12 years age range.^17^ For ages 2 and 3 years, a version of the EQ-5D-Y with modified wording is used, developed in an Australian study (currently in submission) and has been translated with the help of the EuroQol offices. For ages 4–12 years, the EQ-5D-Y is used (proxy version for up to 8 years, self-complete version for 8–12 years), validated in this age group.^18 19^Parental anxiety up to 1 month after discharge, measured by digital questionnaires at discharge, 7 days and 28 days after discharge by the anxiety items on Hospital Anxiety and Depression Scale.^20^Overall paediatric health was measured by digital questionnaires of International Consortium for Health Outcome Measurement (ICHOM) Patient-Reported Outcomes Measurment Information System (PROMIS) set at discharge, 7, 28 and 90 days follow-ups.

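### Randomised children whose primary outcome time is missing because of PICU transfer are excluded from a primary analysis labelled intention-to-treat, which can bias the difference in hours in either direction

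*Protocol article*

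**What the plan says.** Four places in the protocol article bear on this.

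- Primary study parameter(s): "The primary analysis will be conducted on an intention-to-treat basis". The difference in hours is estimated "using a multilevel linear regression model for hospitals". On sensitivity: "Sensitivity analysis will include a per-protocol analysis of the primary outcome".
- Missing data: there are two rules for a missing outcome time. If the time was simply not noted, it is derived from the time of discharge. If it is missing "because the child was transferred to the PICU, these patients are excluded from the primary analysis"; they stay in the safety analyses. The section also names a complete-case sensitivity analysis.
- Control group (under Interventions): children moved to a PICU "will be analysed according to protocol and included in the safety analyses".
- Safety outcomes: the first item is "Number of PICU admissions".

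The endpoint itself is "the time from admission to when all prespecified discharge criteria are met".

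**The concern.** An intention-to-treat comparison keeps each randomised child in the assigned arm whatever happens next. The PICU rule removes children because of something that happens next. That event is one the trial is meant to compare between arms, and the decision is taken by clinicians who know the allocation. The primary comparison is then made among children who did not deteriorate to the point of transfer, and randomisation no longer guarantees that those two groups are alike.

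Nor is the time missing in the usual sense. A child in the PICU has not yet met the discharge criteria, so the clock is still running.

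The trial asks whether a lower threshold shortens stay safely. Under this rule the gain in hours is estimated with some of the children who had a listed harm left out. The PICU count is reported separately, but that does not correct the estimate in hours.

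**Working it through.** **1. The plan's own figure.** Sample size and feasibility gives a 12 h difference, SD 48 h, alpha 0.05 and 80% power. The normal formula gives 2 × (1.960 + 0.842)² × 48²/12² = 2 × 7.849 × 16 = 251.2 per arm; the t-based version gives 252. The article states 251. With 10% dropout, 502/0.9 = 557.8, so 558 against 560 stated. The sample size reproduces and is not at issue. The planning standard error of the difference is 48 × √(2/251) = 4.28 h.

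**2. The passages side by side.** Primary study parameter(s) promises intention-to-treat. Missing data removes a subset defined by a post-randomisation event. Per-protocol and complete-case analyses can only keep the same children or fewer. The Control group wording does not restore them.

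**3. Size.** The article gives no PICU rate and no PICU time, so these are assumptions. Let p92 and p88 be the shares excluded in each arm, M the mean time of those children (same in both arms), and 72 h and 60 h the ward means (the planning mean, and that mean less 12 h).

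- Gain reported after exclusion = 72 − 60 = 12.0 h
- Gain over all randomised = [(1 − p92) × 72 + p92 × M] − [(1 − p88) × 60 + p88 × M]
- Overstatement = (p88 − p92) × (M − 72) + 12 × p88

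| p92 | p88 | M (h) | 92% arm mean | 88% arm mean | Gain, all randomised | Overstatement |
|---|---|---|---|---|---|---|
| 4% | 6% | 144 | 74.88 | 65.04 | 9.84 | 2.16 |
| 4% | 6% | 192 | 76.80 | 67.92 | 8.88 | 3.12 |
| 4% | 8% | 144 | 74.88 | 66.72 | 8.16 | 3.84 |
| 4% | 8% | 192 | 76.80 | 70.56 | 6.24 | 5.76 |
| 2% | 2% | any | – | – | 11.76 | 0.24 |
| 5% | 5% | any | – | – | 11.40 | 0.60 |
| 5% | 3% | 144 | 75.60 | 62.52 | 13.08 | −1.08 |
| 5% | 3% | 192 | 78.00 | 63.96 | 14.04 | −2.04 |

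The sign turns once (p92 − p88) × (M − 72) exceeds 12 × p88. A wider grid with twice the rate in the 88% arm runs from an overstatement of 1.44 h (2% v 4%, M = 120) to 9.60 h (5% v 10%, M = 240).

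**4. No effect on the ward.** If ward children average 72 h in both arms, the exclusion analysis shows 0 h. The all-randomised difference is (p88 − p92) × (M − 72): a lengthening of 1.44–2.40 h at 4% v 6% and 2.88–4.80 h at 4% v 8%, for M = 144–192 h.

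**5. Error rate, illustrative only.** A simulation used 252 per arm, gamma times with mean 72 and SD 48 h, no underlying difference, transfers drawn mainly from the slowest children, and 72 h added per transfer. A significant result favouring the 88% arm (nominal 2.5%) occurred in 2.6% of runs at 3% v 3%, 6.7% at 3% v 6% and 10.9% at 5% v 10%. At 3% v 6% the exclusion analysis averaged 1.9 h in favour of the 88% arm, while the all-randomised mean was 2.3 h against it.

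**The case against.** Several points on the other side stand and limit the claim.

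- **Scope.** A reader might infer that every transferred child is dropped. The rule is conditional: it covers children whose time is missing because of the transfer. One with a recorded time is not clearly excluded.
- **Direction.** A reader might infer that transfer depends on allocation and that the 88% arm will look faster than it is. Nothing in the article shows that transfers differ by arm. At equal rates the bias is small, and with enough fewer transfers in the 88% arm it reverses. Nor does the article give PICU times, so longer times among these children are plausible but not documented.
- **A three-way contradiction.** The Control group wording can be read as handled in the way this protocol lays down, and its ending matches Missing data. It is ambiguous; the clear clash is between Primary study parameter(s) and Missing data.
- **Concealment.** The plan does not hide the harm. PICU transfers are analysed by Poisson regression under intention-to-treat, PICU admissions are reported within 24 hours, a DSMB oversees the trial, and time to discharge has its own Cox analysis with no stated PICU exclusion. An imbalance would be visible, although the primary estimate would stay uncorrected.
- **Size against noise.** In the 4% v 6% case the overstatement, 2.2–3.1 h, is below the planning standard error of 4.28 h. But bias adds to sampling error and does not average out.

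The main defence of substance is that PICU children follow local PICU thresholds, so their later time no longer reflects the assigned threshold. That describes a departure from assigned treatment, and intention-to-treat counts such departures.

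**Conclusion.** The concern holds in this form: a prespecified post-randomisation exclusion, tied to a listed safety outcome, sits inside a primary analysis labelled intention-to-treat, and no named sensitivity analysis undoes it. The article states the rule outright, so this is not a detail left to an unseen analysis plan.

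Whether it changes the result depends on transfer rates that the article does not give. Under the assumed ward and PICU times, a 2-point excess in the 88% arm takes 2.2–3.1 h off a reported 12.0 h gain and a 4-point excess takes off 3.8–5.8 h. Equal rates of 2–5% cost 0.6 h or less, and 5% v 3% the other way means that the plan understates the gain by 1.1–2.0 h. These figures take every PICU child's time as missing and the same mean PICU time in both arms. Twelve hours is the article's own mark of clinical relevance, so shifts of this order can matter. Because the direction is unknown, the rule should be settled before the data are seen.

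**What to change.** - **Missing data:** remove the exclusion. Keep every randomised child in the primary analysis as randomised, with the clock running through the PICU stay until the discharge criteria are met. If that time is not recorded, derive it from final hospital discharge, as the section already does for times that were not noted.
- **Sensitivity analyses:** the gap between meeting the criteria and leaving hospital, estimated from children with recorded times, may not suit PICU children. Add an analysis that gives them the longest observed time or a worst rank. Report the exclusion analysis only as a sensitivity analysis.
- **Control group:** reword to say that transferred children are analysed as randomised, so that this section, Primary study parameter(s) and Missing data agree.

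No clinical procedure changes. Length of stay is already a secondary outcome and PICU admissions are already reported, so the extra work is retrieving end-of-stay times for a small number of children. With 280 per arm, that is about 28 at 4% v 6% (11.2 + 16.8) and 34 at 4% v 8% (11.2 + 22.4). Some may finish their stay away from the study ward, which makes retrieval harder. The estimate may become slightly noisier or less favourable.
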